# Does Perineural Clonidine Prolong the Duration of an Adductor Canal Block When Controlling for Possible Systemic Effects?

- A Randomized Paired Trial in Healthy Volunteers  
SM1-JH-14, EudraCT 2014-005640-18, VEK nr SJ-437

- The difference in duration of sensory block between ACB with ropivacaine + clonidine versus ACB with ropivacaine + placebo, measured as time from block performance (removal of the needle) until pain during tonic heat stimulation returns to baseline values ( $\pm 10$  mm on a Visual Analogue Scale (VAS)).
- The difference in duration of sensory block between ACB with ropivacaine + clonidine versus ACB with ropivacaine + placebo, measured as time from block performance (removal of the needle) until warmth detection threshold (WDT) returns to baseline values ( $+2^{\circ}\text{C}$  or below).
- The difference in duration of sensory block between ACB with ropivacaine + clonidine versus ACB with ropivacaine + placebo, measured as time from block performance (removal of the needle) until pain heat pain detection threshold (HPDT) returns to baseline values ( $+2^{\circ}\text{C}$  or below).
- The difference in maximum pain score (VAS) during tonic heat stimulation of the skin (30 seconds at  $45^{\circ}\text{C}$ ) between ACB with ropivacaine + clonidine versus ACB with ropivacaine + placebo, at 4 hours post block.
- The difference in maximum pain score (VAS) during tonic heat stimulation of the skin (30 seconds at  $45^{\circ}\text{C}$ ) between ACB with ropivacaine + clonidine versus ACB with ropivacaine + placebo, at 1 hour after resolution of the block (rebound pain).

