## Participants completion and interruption of trial

- A participant has completed the trial, when the treatment plan has been followed until one hour after the alcohol-swab again is perceived as cold (normal temperature discrimination).
- A participant who interrupts the trial, is a participant who is included in the trial and has given written informed consent, but has not completed the trial, whether trial medication was given or not. If a participant does not complete the trial, or drops out, a follow-up plan must be stated on if and how data is collected.

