Does Perineural Clonidine Prolong the Duration of an Adductor Canal Block When Controlling for Possible Systemic Effects?  
- A Randomized Paired Trial in Healthy Volunteers  
SM1-JH-14, EudraCT 2014-005640-18, VEK nr SJ-437

and forth the tests are done every hour until values are normalized/returned to baseline. If necessary after the first 4 hours there will be given opportunity to sleep and sensory tests as well as blood pressure measurements (if subjects have stabile blood pressure) is omitted here.

- WDT and HPDT are performed at T=1h. If pain score during tonic heat stimulation equals 0 WDT and HPDT are omitted. When pain score during tonic heat stimulation again is > 0, WDT and HPDT are performed every hour until the values have normalized.
- Similarly, temperature discrimination testing with an alcohol swab is performed every half hour if the pain score during tonic heat stimulation is > 0.
- The individual test finishes when the value has returned to baseline.
- A participant is defined as a non-responder and withdrawn from the trial if normal temperature discrimination and pin-prick persists in one or both legs 2h after block performance.
- A block is defined as partial if there is a reduced sensitivity to cold (alcohol swab) and pin-prick, but VAS > 0 tonic heat stimulation at t = 2h.
- Side effects from t=0 until discharge is recorded in the CRF.
- When all values are normalized the trial is terminated and the participant sent home.

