## Clinical assessments

### Generally:

- All tests are done on the right leg first, followed by the left leg.
- Sensory tests will be performed with the participants in a semi-recumbent position in a room solely used for the trial.
- The tests are done in the following order (all tests are not necessarily done at all times): Temperature discrimination test, Pinprick, WDT, HPDT and Pain during tonic heat stimulation.
- The sensory tests are done on the anteromedial aspect of the lower leg (crus) in the area supplied by the saphenous nerve.
- WDT, HPDT and Pain during tonic heat stimulation is measured using a computer controlled thermode (2,5 cm^2, Thermotest, Somedic A/B, Hörby, Sweden).
- WDT and HPDT are determined from the average of four consecutive measurements. A 10-20 second pause will be held between each of the consecutive measurements.
- Pain during tonic heat stimulation is considered normalized when max VAS returns to baseline  $\pm$  10 mm. WDT and HPDT are considered normalized when returned to baseline + 2 ° C or less.

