## STATISTICAL ANALYSIS

### Sample size calculation

Does Perineural Clonidine Prolong the Duration of an Adductor Canal Block When  
Controlling for Possible Systemic Effects?  
- A Randomized Paired Trial in Healthy Volunteers  
SM1-JH-14, EudraCT 2014-005640-18, VEK nr SJ-437

A few studies have compared the duration of perineural clonidine with systemic clonidine, but these studies have examined combination with bupivacaine(4, 21), mepivacaine(3) and levobupivacaine(22) and not perineural ropivacaine. El Saied (9) investigated ropivacaine with clonidine as an adjuvant perineurally vs. ropivacaine alone in a study with 50 patients. The addition of clonidine as an adjuvant prolonged the sensory blockade 489-628 minutes (95% CI 90-187). In a yet unpublished study by our group on healthy volunteers, we found a sensory duration of an ACB with 20ml ropivacaine 5 mg/ml of 22 (SD 4) hours. Accordingly, we find that a 240 minutes prolongation of block duration will be clinically relevant. With a type 1 error risk of 5% and a type 2 error risk of 10% and an SD of 240 minutes, a total of 18 subjects is needed in this paired trial to show a difference of 240 minutes. In order to compensate for possible dropouts, we plan to include 21 participants.

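### The rules for ending tests and the trial day conflict with the rebound-pain outcome, which needs a tonic-heat score on each leg 1 hour after block resolution

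*Protocol*

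**What the plan says.** Four places in the protocol bear on this.

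- **Secondary outcome measures.** The last one listed is the between-leg difference in maximum VAS during tonic heat (45 °C for 30 seconds), taken "at 1 hour after resolution of the block (rebound pain". The text does not say which test defines resolution here.
- **Participants completion and interruption of trial.** A participant has completed when the plan has been followed "until one hour after the alcohol-swab again is perceived as cold (normal temperature discrimination". The leg is not named.
- **Trial schedule for the participants.** From 4 hours on, "the tests are done every hour until values are normalized/returned to baseline". Then: "The individual test finishes when the value has returned to baseline". The day ends with "When all values are normalized the trial is terminated and the participant sent home".
- **Clinical assessments, Generally.** "Pain during tonic heat stimulation is considered normalized when max VAS returns to baseline", with a tolerance of 10 mm either way.

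**The concern.** The rebound score has to be taken after recovery. The schedule stops testing at recovery and contains no later tonic-heat test. Staff who work from the schedule would have no instruction to take the measurement in a leg whose tonic-heat pain is already normal, and would have an instruction to let the participant go once every test is normal.

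Two things are at stake. The first is the number of complete pairs, because the outcome is a within-person difference and needs both legs. The second is selection. Under the per-test rule, a leg is still being tested 1 hour after swab return only if its tonic-heat VAS had not entered the band by then, so whether the score exists depends on the variable being measured. Under the end-of-day rule, the later-resolving leg is the one most likely to go unmeasured. If clonidine prolongs the block, that is usually the clonidine leg. No analysis can recover a VAS that was never taken.

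**Working it through.** The protocol gives no figure to reproduce. The check is a comparison of the rules, followed by an illustration of what the schedule would yield if it were applied without the completion rule.

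**Rules side by side**

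| Question | Secondary outcome | Completion rule | Trial schedule |
|---|---|---|---|
| When does observation end? | Not before resolution + 1 h | Swab return + 1 h | All values normal |
| Which leg starts the hour? | Each leg, by implication | Not stated | No such hour |
| Tonic heat at + 1 h if already normal? | Required | Not stated | Test already finished |

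The completion rule supplies the hour, but it refers back to the treatment plan, and that plan is what ends the test.

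**Illustration: inputs**

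- From Sample size calculation: "we found a sensory duration of an ACB with 20ml ropivacaine 5 mg/ml of 22 (SD 4) hours", and "a 240 minutes prolongation of block duration will be clinically relevant" (4 h).
- From the schedule: an hourly test grid.
- Assumed, not in the protocol: between-leg correlation ρ of 0 or 0.5; a true effect of 0 or 4 h; and a lag from swab return to tonic-heat normalisation that is either fixed at 0 h or has mean −1, 0 or +1 h with SD 1 h, independent between legs.

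**(a) End-of-day rule only, all tests in a leg recovering together (lag 0).** The last leg to recover ends the day, so it never has a + 1 h reading and complete pairs are 0%. The other leg has a reading if it recovers at least one grid step earlier. The SD of the between-leg difference is 4 × √(2(1 − ρ)), which is 5.66 h for ρ = 0 and 4 h for ρ = 0.5. One grid step corresponds to a difference of roughly 0.5 h. With a 4 h effect:

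- placebo leg measured: Φ((4 − 0.5)/5.66) = Φ(0.62) = 0.73, or Φ(3.5/4) = Φ(0.875) = 0.81;
- clonidine leg measured: Φ((−4 − 0.5)/5.66) = Φ(−0.80) = 0.21, or Φ(−4.5/4) = Φ(−1.125) = 0.13.

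A simulation of 200,000 participants gives the same values: 73–81% of placebo legs and 13–21% of clonidine legs. With no effect, each leg is measured in 45–46%. When the lag varies, complete pairs rise to about 7%, 33% and 72–74% for mean lags of −1, 0 and +1 h.

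**(b) Per-test stopping rule applied as well.** A leg has a reading only if its lag rounds to 1 h or more, that is, exceeds 0.5 h.

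| Mean lag | One leg | Both legs | Pairs out of 18–21 |
|---|---|---|---|
| −1 h | Φ(−1.5) = 0.07 | under 0.01 | about 0 |
| 0 h | Φ(−0.5) = 0.31 | 0.31² = 0.10 | about 2 |
| +1 h | Φ(0.5) = 0.69 | 0.69² = 0.48 | about 9–10 |

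The simulation gives 0%, 9–10% and 48%.

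**(c) Completion rule honoured for both legs and tonic heat repeated at + 1 h.** These rules then cause no loss.

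**The case against.** The strongest reply is that the completion rule exists for this measurement. Its hour matches the rebound time point, the outcome itself names the stimulus, and Sensory tests defines block duration by the swab. A team reading these parts together would probably keep the participant and take the score. That stands as far as intent goes, and it means loss cannot be stated as fact. It does not remove the conflict: the hour is not tied to a leg, although the trial is planned around a 4 h difference between legs, and nothing overrides the instruction that a finished test stays finished.

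A reader might infer three stronger points that the protocol does not support.

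- **An upward-biased rebound estimate.** The band runs both ways. A leg still outside it may be below baseline because it is still partly numb, so retained scores could be low as well as high.
- **Right-censoring of the other secondary durations at swab return + 1 h.** This needs the completion rule to cut testing short. That rule defines who counts as a completer, and the schedule continues tests until values are normal.
- **An error in comparing raw VAS.** Side is randomised within person, so the unadjusted paired comparison is valid. Baseline adjustment is a precision choice.

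**Conclusion.** The protocol contradicts itself on when observation ends, and it does not schedule the test that one of its secondary outcomes needs. If the trial schedule is followed as written, the rebound comparison may have few complete pairs, drawn mainly from legs slow to normalise. The loss would tend to fall on the later-resolving leg.

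The size cannot be fixed from the protocol. Across the lags assumed above, complete pairs run from 0% to about 74% under the end-of-day rule alone and from 0% to about 48% when the per-test rule also applies. All of these figures set the completion rule aside. No single count of surviving pairs is defensible, and the direction of bias is unknown. The matter concerns one secondary outcome; the primary outcome, time to swab return, is untouched. It is still worth correcting before the first participant, because it decides whether the data are collected at all.

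**What to change.** Reconcile the completion rule and the trial schedule in three steps.

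1. **One end-of-observation rule in both sections.** Observation for trial measurements ends at the later of (i) all modalities normal in both legs and (ii) 1 hour after swab return in the later-resolving leg.
2. **Define resolution for the rebound outcome** as each leg's own swab return.
3. **Add the test to the schedule.** Tonic heat is measured on each leg 1 hour after that leg's swab return, even if the test has already met its stopping rule.

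Optionally, adjust the paired VAS difference for the paired difference in baseline VAS, which is already collected. This may gain precision and corrects no error.

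The cost is one 30-second stimulus per leg and up to about one more hour for some participants, an hour the completion rule already contemplates. At the stated 150 DKK per hour, the upper limit is 21 × 1 × 150 = 3,150 DKK.

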## Clinical assessments

### Generally:

- All tests are done on the right leg first, followed by the left leg.
- Sensory tests will be performed with the participants in a semi-recumbent position in a room solely used for the trial.
- The tests are done in the following order (all tests are not necessarily done at all times): Temperature discrimination test, Pinprick, WDT, HPDT and Pain during tonic heat stimulation.
- The sensory tests are done on the anteromedial aspect of the lower leg (crus) in the area supplied by the saphenous nerve.
- WDT, HPDT and Pain during tonic heat stimulation is measured using a computer controlled thermode (2,5 cm^2, Thermotest, Somedic A/B, Hörby, Sweden).
- WDT and HPDT are determined from the average of four consecutive measurements. A 10-20 second pause will be held between each of the consecutive measurements.
- Pain during tonic heat stimulation is considered normalized when max VAS returns to baseline  $\pm$  10 mm. WDT and HPDT are considered normalized when returned to baseline + 2 ° C or less.

### Sensory tests:

- **Temperature discrimination test:** With this test, we wish to register the duration of sensory nerve block where the stimulation of the skin with an alcohol swab does not feel cold. The duration of the nerve block is defined as time from block performance (removal of the needle) until stimulation of the skin with an alcohol swab feels cold again.

## Does Perineural Clonidine Prolong the Duration of an Adductor Canal Block When Controlling for Possible Systemic Effects?

- A Randomized Paired Trial in Healthy Volunteers  
SM1-JH-14, EudraCT 2014-005640-18, VEK nr SJ-437

- **Pinprick test:** Determination of duration of sensory nerve block defined as the inability to distinguish blunt from sharp when stimulated with a needle. This test determines the duration of the nerve block defined as time from block performance (removal of the needle) until the indentation of the skin with a needle again feels sharp.
- **Maximum pain during tonic heat stimulation:** During this test, the participants' skin is heated to 45 °C for 30 seconds. The participants rates the pain elicited on a Visual Analogue Scale (VAS) using a ruler indicating "no pain" = 0 mm at one end, and "worst perceivable pain" = 100 mm at the opposite end. The duration of the nerve block measured by pain during tonic heat stimulation is defined as time from block performance (removal of the needle), until the tonic heat stimulation again elicits a painful response i.e. VAS >0.
- **Determination of warmth threshold (WDT)** represents the lowest temperature perceived as warm. Start temperature for the thermode is 32 ° C. The temperature rises by 1 ° C/sec during the threshold determination and 5 ° C/sec at the return to the starting temperature after the test. The participant is asked to press a button when the thermode feels warm while also finishing heat stimulation. If the limit of temperature increase beyond 52 ° C before recording a threshold value the thermode automatically returns to its starting temperature and 52 ° C is recorded. Each threshold value is calculated as the average of four stimulations; stimulations are presented 6-10 seconds apart. The duration of sensory block assessed by WDT, defined as the time from block performance until WDT is normalized.
- **Determination of heat-pain threshold (HPDT)** represents the lowest temperature perceived as painful. Start temperature for the thermode is 32 ° C. The temperature rises by 1 ° C/sec during the threshold determination and 5 ° C/sec at the return to the starting temperature after the test. The participant is asked to press a button, when the thermode feels painful while also finishing heat stimulation. If the limit of temperature increase beyond 52 ° C before recording a threshold value the thermode automatically returns to its starting temperature and 52 ° C is recorded. Each threshold value is calculated as the average of four stimulations; stimulations are presented 6-10 seconds apart. The duration of sensory block assessed by HPDT, defined as the time from block performance until HPDT is normalized.

The trial lasts from the introduction until the nerve block wears off (typically 10-14 hours). The participants will receive the above-mentioned treatments according to a computer-generated randomization list.

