Nerve blocks are a well-established treatment for surgery and pain relief, and a follow-up study of patients after receiving adductor channel blocks showed no signs of nerve damage 3-6 months after surgery (28). The models used in the study is validated in other medical specialties, and the discomfort experienced is normally only perceived as mild.

A study on isolated sensory neurons from rats showed that clonidine was not associated with increased cell death when used as an adjuvant for ropivacaine (29).

Does Perineural Clonidine Prolong the Duration of an Adductor Canal Block When  
Controlling for Possible Systemic Effects?  
- A Randomized Paired Trial in Healthy Volunteers  
SM1-JH-14, EudraCT 2014-005640-18, VEK nr SJ-437

The aim of the trial is to investigate if clonidine used as an adjuvant to ropivacaine prolongs the duration of a single-shot nerve block by a peripheral mechanism when controlling for systemic effects. Our hypothesis is, that the perineural injection of clonidine as an adjuvant to ropivacaine prolongs the duration of an ACB compared to ropivacaine + placebo.

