## METHODOLOGY

### General treatment plan and medical dosing

### Trial schedule for the participants:

Does Perineural Clonidine Prolong the Duration of an Adductor Canal Block When Controlling for Possible Systemic Effects?  
- A Randomized Paired Trial in Healthy Volunteers  
SM1-JH-14, EudraCT 2014-005640-18, VEK nr SJ-437

- Information about the project is given by the principal investigator. Time for questions and consideration will be provided.
- The principal investigator [name] (MD) or sub investigator (MD) obtains a short medical history according to the Case Report Form going through in- and exclusion criteria. Height, weight Blood pressure and Pulse are measured.
- All sensory and motor modalities are tested on the participants to familiarize them with the procedures.
  - Temperature-discrimination test with an alcohol swab
  - Pin-prick test
  - Pain during tonic heat stimulation (baseline value is measured)
  - Warmth detection threshold (WDT)
  - Heat pain detection threshold

Baseline measurements are done for all modalities.

- **Ultrasound guided ACB:**

- The ACB is performed using ultrasound guidance as a single injection of local anesthetics next to the saphenous nerve in the adductor canal at a mid-thigh level.
- The ACB's are performed on the RIGHT side first followed immediately by the opposite treatment on the LEFT side according to randomization.
- All participants receive both treatments, one in each leg.

- **Trial medication:**

- **Treatment A:** ACB with 20 ml ropivacaine 0,5 % + 1,0 ml clonidine 150 µg/ml
- 
- **Treatment B:** ACB with 20 ml ropivacaine 0,5 % + 1,0 ml isotonic saline
- **No other medication is planned during the trial period.**
- Time of block performance (removal of needle) in the right arm is registered as T=0.
- The participants are monitored with continuous ECG, pulse oximetry and blood pressure every 15 minutes for 4 hours after administration of the trial medication.
- Sedation is measured every hour post block using a verbal rating scale (VRS) from 0-3 (0 no sedation, 1 light sedation, 2 moderate sedation, 3 pronounced sedation).
- Temperature discrimination test with an alcohol swab, pin-prick and tonic heatstimulation is performed at T=1h and 4h post block. If temperature discrimination is retained at t = 1h the sensory tests are also done at t = 2h and t = 3h. From 4 h

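### Tonic-heat block duration has two conflicting end points, and the ±10 mm rule can score a fully blocked leg as recovered when its baseline VAS is 10 mm or less

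*Protocol*

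**What the plan says.** Three places in the Protocol fix the end of block on the tonic-heat test.

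- Secondary outcome measures: duration runs from needle removal "until pain during tonic heat stimulation returns to baseline values", with a tolerance of ±10 mm on the VAS.
- Clinical assessments, Generally: "Pain during tonic heat stimulation is considered normalized when max VAS returns to baseline", again ±10 mm.
- Sensory tests, maximum pain during tonic heat stimulation: duration on this test is defined as the time from needle removal "until the tonic heat stimulation again elicits a painful response i.e. VAS >0".

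Four further statements bear on how these rules work.

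- The VAS runs from 0 mm (no pain) to 100 mm (Sensory tests).
- VAS 0 is treated as the blocked state: "A block is defined as partial if there is a reduced sensitivity to cold (alcohol swab) and pin-prick, but VAS > 0 tonic heat stimulation" (Trial schedule for the participants, assessed 2 h after the block).
- The stopping rule is "The individual test finishes when the value has returned to baseline" (same section).
- A baseline is taken, but the inclusion and exclusion criteria set no minimum for it.

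**The concern.** The same outcome, on the same test and from the same time zero, ends at two different events. An analyst following the outcome list and one following the test description could report different durations from the same case report forms, and the choice could be made after the data are seen.

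The ±10 mm rule also has a defect of its own at the floor of the scale. VAS cannot fall below 0, so when baseline pain is low, no pain at all is within 10 mm of baseline. A densely blocked leg then meets the rule for recovery. Since the individual test ends once its value is back to baseline, the later return of pain may never be recorded for that leg.

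A lesser concern lies at the upper limit. A VAS more than 10 mm above baseline is outside the window, so it counts as not yet normalized although sensation has plainly returned.

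**Working it through.** No sample size or power figure is involved, so there is no stated figure to reproduce. The check compares the rules and then applies arithmetic to the window.

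**Inputs.** Baseline VAS of the leg, B (mm; no value in the Protocol, so a range is shown). Tolerance 10 mm (Secondary outcome measures; Generally). Scale floor 0 mm (Sensory tests). First post-block test at 1 h, with hourly tests from 4 h until values normalize (Trial schedule).

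**Step 1: lowest VAS that counts as recovered.** Under ±10 mm it is max(0, B − 10). Under the other rule it is any VAS above 0.

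| B (mm) | ±10 mm window (mm) | Is VAS 0 inside? |
|---|---|---|
| 0 | 0 to 10 | yes |
| 5 | 0 to 15 | yes |
| 10 | 0 to 20 | yes |
| 11 | 1 to 21 | no |
| 20 | 10 to 30 | no |
| 30 | 20 to 40 | no |
| 60 | 50 to 70 | no |

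VAS 0 is inside the window when 0 ≥ B − 10, that is, exactly when B ≤ 10.

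**Step 2: B ≤ 10 mm.** A leg at VAS 0 meets ±10 mm at the 1 h test, while under VAS >0 it is still blocked. For scale, the Protocol elsewhere puts the time for the block to wear off at typically 10–14 hours (end of Sensory tests) and cites a sensory duration of 22 (SD 4) hours (Sample size calculation). Neither is tied to the tonic-heat test. With B = 0, the VAS >0 rule has its own gap: its end point might never be reached.

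**Step 3: B > 10 mm.** Any VAS inside the window is above 0, so VAS >0 is met no later than ±10 mm. To illustrate the gap, assume VAS rises linearly from 0 to B over R hours (R is an assumption; the Protocol gives none). VAS >0 is met at the start of the rise and B − 10 is reached after R × (B − 10)/B hours, so that is the gap:

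| B (mm) | R = 1 h | R = 2 h | R = 4 h |
|---|---|---|---|
| 20 | 0.50 h | 1.00 h | 2.00 h |
| 30 | 0.67 h | 1.33 h | 2.67 h |
| 40 | 0.75 h | 1.50 h | 3.00 h |
| 60 | 0.83 h | 1.67 h | 3.33 h |

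These are gaps in continuous time. With hourly tests, a gap under 1 h is recorded as either 0 or 1 h, depending on where the tests fall.

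**Step 4: upper limit.** The end point is the first test inside a window 20 mm wide (when B ≥ 10). A return of pain is missed only if VAS goes from below B − 10 at one test to above B + 10 at the next. For B = 30 that means from below 20 mm to above 40 mm between consecutive tests, or across a sleep break in which tests are omitted.

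**The case against.** The strongest reply is that VAS >0 was meant only as a testing trigger. The Trial schedule uses it to start half-hourly swab tests and to resume WDT and HPDT. That explains where the phrase may have come from, but Sensory tests states it outright as the definition of duration, so the conflict stands.

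Next, a value can only return to baseline after leaving it. For B ≤ 10 mm and VAS 0 the time is then arguably undefined rather than 1 h. This is fair as a reading, but it leaves the outcome without a value instead of with a wrong one. The Generally section also calls such a value normalized without requiring that it ever left the window.

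Third, for B > 10 mm tests continue hourly until baseline is regained, so both durations can be derived from the recorded data. That stands: in those legs the conflict is one of definition, not of lost data.

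Fourth, evaluability of low-baseline legs might be settled in a statistical analysis plan, which is not at hand, and Data handling has assessability decided before the code is broken. Neither removes the contradiction inside the Protocol, and a later plan cannot recover tests that were stopped.

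Some stronger readings go too far:

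- A reader might infer that the two rules always differ by at least one test interval. They need not: if VAS passes from 0 to B − 10 or more between two tests, both are met at the same test.
- A reader might infer that rebound pain generally lengthens recorded duration. It does so only under the jump in step 4, and nothing in the Protocol suggests how often that occurs.
- A reader might infer that a low baseline always forces a zero difference between legs. That needs a low baseline in both legs; baselines may differ by leg.

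**Conclusion.** The point holds as a conflict of definition on one secondary outcome, together with an exact floor defect in one of the two definitions. The threshold of 10 mm follows from the scale and the tolerance alone.

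For baselines above 10 mm the two end points may coincide or differ; with linear recovery over 1 to 4 h, an assumption, the gap is 0.50 to 3.33 h for baselines of 20 to 60 mm. For a leg at or below 10 mm the recorded duration can be as short as 1 h under full block. The frequency of such baselines cannot be computed. The Background says of the models used that "the discomfort experienced is normally only perceived as mild", which makes low values plausible but is not a VAS figure. With 21 participants planned, a few such legs could matter to this outcome.

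A reader might infer that the primary outcome is compromised. The documents do not support that: its definition rests on the alcohol swab alone. At most, if tonic-heat testing stops early in a low-baseline leg, the VAS >0 trigger for half-hourly swab tests may go unobserved, which affects the spacing of tests and not the definition. The matter should be corrected, but it does not threaten the trial's main comparison.

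**What to change.** Use one definition in Secondary outcome measures, in Generally and in Sensory tests, one-sided like the WDT and HPDT rules:

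- Tonic-heat duration ends at the first test with VAS >0 and VAS at or above baseline minus 10 mm, judged per leg against that leg's own baseline. For baselines above 0 and up to 10 mm this reduces to VAS >0, so no separate low-baseline rule is needed. A VAS that jumps past the upper limit counts as recovered.
- A leg with baseline VAS 0 is declared not evaluable for this outcome before unblinding.
- The stopping sentence in the Trial schedule is aligned, so that tonic-heat testing continues until this end point is met.

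The cost is wording, continued hourly tonic-heat tests in low-baseline participants who would otherwise have stopped, and possibly a few participants not evaluable for one secondary outcome.

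### HPDT readings at the 52 °C cut-off are averaged as real thresholds, so the baseline + 2 °C recovery rule cannot register persisting block when baseline HPDT is 50 °C or more

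*Protocol*

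**What the plan says.** Four rules in the Protocol act together on HPDT duration.

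- **Ceiling.** Under Sensory tests, an HPDT run that passes 52 °C before the participant responds is stopped: "the thermode automatically returns to its starting temperature and 52 ° C is recorded". That value then enters the mean: "Each threshold value is calculated as the average of four stimulations".
- **Recovery.** Under Clinical assessments (Generally): "WDT and HPDT are considered normalized when returned to baseline + 2 ° C or less". The secondary outcome uses the same margin; its time runs "until pain heat pain detection threshold (HPDT) returns to baseline values", with +2 °C or below given in brackets. Sensory tests closes the definition: "The duration of sensory block assessed by HPDT, defined as the time from block performance until HPDT is normalized".
- **Stopping.** In the trial schedule for the participants: "The individual test finishes when the value has returned to baseline".
- **Tonic-heat condition.** The same schedule says "WDT and HPDT are performed at T=1h", followed at once by "If pain score during tonic heat stimulation equals 0 WDT and HPDT are omitted". Hourly testing resumes once the tonic-heat score is above 0 again. The fixed test order under Generally puts HPDT before tonic heat.

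No upper limit is set on baseline HPDT in the inclusion criteria, the exclusion criteria or the baseline step. Nothing says that a cut-off reading cannot count as normalized.

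**The concern.** A run that ends at the cut-off shows only that the pain threshold was not reached by 52 °C. It is a censored observation, but the Protocol stores it as a threshold of exactly 52 °C and averages it with real ones. With a recovery margin of 2 °C, the ceiling falls inside the recovery zone of any leg with a high enough baseline. In such a leg the rule can only answer *recovered*.

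The stopping rule makes this hard to repair. Once a session is judged normalized, HPDT is not tested again in that leg, so the true return time is not observed and cannot be recovered at analysis. Because the comparison is within pairs, a false stop in one leg only would create a spurious difference in either direction, depending on which leg received clonidine.

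**Working it through.** **Inputs.** Cut-off value 52 °C and mean of four readings (Sensory tests); margin + 2 °C (Secondary outcome measures; Generally); 21 participants, hence 42 legs (Study design). The Protocol states no figure on this point that could be reproduced.

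**Step 1: all four readings at the cut-off.** The session mean is 52. It passes when 52 ≤ b + 2, that is, when baseline b ≥ 50.

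| Baseline (°C) | Limit (°C) | A mean of 52 counts as |
|---|---|---|
| 49 | 51 | not recovered |
| 49.9 | 51.9 | not recovered |
| 50 | 52 | recovered |
| 51 | 53 | recovered |

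**Step 2: k of four at the cut-off, the rest at baseline.** The session passes when (52k + (4 − k)b)/4 ≤ b + 2. This simplifies to k(52 − b) ≤ 8, or b ≥ 52 − 8/k.

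- k = 1: b ≥ 44
- k = 2: b ≥ 48
- k = 3: b ≥ 49.33
- k = 4: b ≥ 50

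For example, at b = 49.5 with three cut-off readings: (3 × 52 + 49.5)/4 = 51.375, against a limit of 51.5, so the session passes.

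**Step 3: when such a reading can be taken.** There are three cases.

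1. *At 1 h, if HPDT is unconditional there.* The first of the two schedule sentences, and the order that puts HPDT before tonic heat, allow this reading. In that order the tonic-heat score of the same session does not yet exist. A numb leg with b ≥ 50 gives 52 °C, passes, and its test ends with a duration of about 1 h.
2. *After the tonic-heat score is above 0 again.* Pain during 30 s at 45 °C does not guarantee a response to a 1 °C/s ramp before 52 °C, so cut-off readings remain possible. The leg is then partly recovered, and the duration is shortened by less.
3. *If the condition applies throughout.* A leg with a baseline of 50 °C or more may score 0 at 45 °C even before any block. HPDT might then never be retested, and its duration would be undetermined.

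**Step 4: how often (assumption).** The Protocol gives no baseline HPDT distribution. Taking it as normal, P(b ≥ 50) = 1 − Φ((50 − mean)/SD).

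| Assumed mean, SD (°C) | P(b ≥ 50) | Expected legs of 42 |
|---|---|---|
| 44, 1.5 | below 0.1% | 0.0 |
| 46, 2 | 2.3% | 42 × 0.0228 = 0.96 |
| 48, 3 | 25% | 42 × 0.2525 = 10.6 |

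The range is too wide to predict how many legs would be affected. It shows only that zero, one or several are all plausible.

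**The case against.** The strongest objection is the tonic-heat condition. A completely numb leg scores 0 on tonic heat, so HPDT is omitted and no false recovery can be recorded while the condition is in force. This stands, and it removes the most alarming version of the problem. A reader might infer that every fully blocked leg with a high baseline will be logged as recovered at 1 h. The documents do not support that, because it requires an unconditional test at 1 h, and the wording leaves that open.

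Two further inferences fail. One is that affected legs would be recorded some 9 to 21 h too short. That range comes from subtracting 1 h from a 10–14 h wear-off time and a 22 h sensory duration. Neither is stated for HPDT, and the subtraction again needs the unconditional test. The other is that a single bad pair would dominate a paired t-test. Data handling provides for the Wilcoxon signed-rank test when normality is violated, which blunts a lone extreme difference.

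It can also be said that ceiling values are analysis-plan detail, and that the Protocol already settles assessability before the code is broken. That is fair for excluding a participant. It does not help here, because the recording, recovery and stopping rules are all in the Protocol, and they determine which readings are ever taken.

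Scope is also limited. HPDT duration is one of six secondary outcomes, and the alcohol-swab primary is untouched. WDT shares the cut-off, but even one cut-off reading among four could pass only from a baseline WDT of 44 °C. I assume that is remote for a warmth threshold measured from a 32 °C start.

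**Conclusion.** The point holds in limited form. From the Protocol's own numbers, the HPDT recovery rule cannot return *still blocked* in a leg with a baseline of 50 °C or more. Sessions with two or three cut-off readings can pass from 48 °C or about 49.3 °C, if the other readings are at baseline. These boundaries are exact.

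The consequence depends on an ambiguity. If HPDT is unconditional at 1 h, a numb leg can be closed at about 1 h. If the tonic-heat condition applies throughout, the error is confined to partly recovered legs and is smaller, while some high-baseline legs may have no determinable HPDT duration. The number of legs involved is unknown: about 0 to 11 of 42 across the assumed distributions, and about 1 in the middle case. The matter is worth correcting because a rule followed as written gives a wrong result for some legs and stops further testing, but it bears materially on a single secondary outcome.

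**What to change.** In Clinical assessments (Generally and Sensory tests), state three things:

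1. A reading that reaches the 52 °C cut-off is recorded as *not felt*, not as a threshold. HPDT is normalized only if the mean of the four readings is at or below baseline + 2 °C **and** none of the four reached the cut-off.
2. Where a baseline reading itself reached the cut-off, HPDT duration is declared not evaluable for that participant. This is decided before the code is broken, at the assessability step already in Data handling.
3. Whether the tonic-heat condition applies at 1 h, so that the trial schedule and the test order agree, and what happens to HPDT in a leg that scores 0 on tonic heat at baseline.

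The change takes a few sentences in the Protocol and a tick box per reading in the CRF, and it must be in place before testing, since omitted readings cannot be recovered. The cost is a few participants lost from the HPDT-duration outcome. Legs with a baseline between 50 and 52 °C also get a somewhat tighter tolerance: at 51 °C all four readings must be below 52 °C, leaving less than 1 °C instead of 2 °C. At lower baselines, one stray cut-off reading would defer normalization to the next hourly test.
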